## 1. Introduction

Tai Chi is a traditional mind-body exercise, which originated from ancient China and widely spread all over the world. It is reported that there are 5 and 150 million Tai Chi practitioners in China and the whole world, respectively. Tai Chi has dual effects on healthcare and treatment. For healthy subjects (HS), the healthcare effects of Tai Chi in strengthening muscle strength [1], improving physical flexibility [2], enhancing the ability to balance and control [2], increasing vital capacity [3], reducing stress [4], and others have long been identified. For patients, the therapeutic effects of Tai Chi for treating multiple chronic diseases including osteoarthritis [5], hypertension [6], type 2 diabetes mellitus [7], coronary heart disease [8], and chronic obstructive pulmonary disease [9] have also been proven by a number of studies. These studies indicated that Tai Chi was widely involved in the prevention, treatment, and rehabilitation of various diseases. Does Tai Chi have different effects on the same organ/system in different practitioners? For example, a systematic review and meta-analysis showed that mind-body interventions, including Tai Chi, were effective in alleviating gastrointestinal symptoms and improving the quality of life (QOL) of patients [10]. Does Tai Chi have different gastrointestinal modulation effects between patients with gastrointestinal disorders and HS? In other words, is the gastrointestinal regulation of Tai Chi disease-oriented and influenced by individual physical condition? However, majority of the Tai Chi-related studies were performed either on patients or HS, and few studies were performed on both patients and HS to investigate the influence of physical conditions on the effect of Tai Chi.

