On the basis of the characteristics of Tai Chi and previous researches, we predict that the effects of Tai Chi include two aspects: the relatively specific effects and nonspecific effects. The nonspecific effects mainly refer to the modulating effects on human motor function (muscle strength, physical flexibility, etc.) and respiratory function, especially vital capacity. The nonspecific effects might also manifest as maintaining the normal function of organs/systems, keeping the body in a relatively balanced and coordinated state. While the relatively specific effects of Tai Chi are disease-oriented, meaning that when the body is in a pathological state, Tai Chi practice might reduce the hyperactive function to improve the hypoactive function.

To test the hypothesis, we design this neuroimaging study. In this study, both functional constipation (FC) patients and HS were selected as participants to investigate the specific effects (gastrointestinal function) and nonspecific effects (motor function and respiratory function) of Tai Chi. FC is a common functional gastrointestinal disorder (FGID) with high prevalence. It is characterized by various constipation-related symptoms, including reduced defecation, defecation stress, hard stools, and uncomfortable abdominal muscle in the absence of evident organic or structural reasons for these symptoms. A randomized control trial indicated that Tai Chi practice could significantly improve the constipation symptom of patients with chronic FC [11].

This study aims to (1) investigate the nonspecific effects of Tai Chi by comparing the influence of Tai Chi practice on motor function and respiratory function between FC patients and HS using the lower-extremity muscle strength test, functional balance tests, and vital capacity test; (2) investigate the specific effects of Tai Chi from three aspects, including gastrointestinal symptom, autonomic nervous activity, and emotional state; and (3) explore the potential central responses of Tai Chi's specific and nonspecific effects by functional magnetic resonance imaging (fMRI).

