### 2.10. Statistical Analysis

#### 2.10.1. Clinical Data Analysis

Clinical data will be analyzed by independent statisticians who do not know the test procedure based on the principles of intention to treat (ITT) and per protocol. The statistical significance threshold has *p* value <0.05. The results of the participants who failed to complete the study will be considered no different from the baseline data in ITT analysis. All continuous variables will be presented as mean ± standard deviation. The categorical variables will be described in percentage (%). The clinical data in the two groups (FC group and HS group) will be compared with two-sample *t*-tests, and the comparisons of the baseline and after intervention in each group will be compared with a paired sample *t*-test. Nonparametric tests (Mann–Whitney *U* test) will be used to compare nonnormally distributed clinical data, and the *χ*^2^ test or Fisher's test will be used to compare categorical variables.

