## 3. Discussion

As a popular physical–mind exercise, Tai Chi is widely used in the prevention, treatment, and rehabilitation of various diseases. On the basis of the characteristics and related studies on Tai Chi, we put forward the original hypothesis that Tai Chi practice can produce relative specific effects and nonspecific effects on the human body.

The main purposes of this study include two aspects. First, this study tries to explore the physiological and psychological existence of the specific and nonspecific effects of Tai Chi by comparing the differences in the motor function, respiratory function, gastrointestinal symptoms, psychological manifestations, and HRV between FC patients and HS after Tai Chi practice. Second, this study tries to explore the potential central mechanism of the specific and nonspecific effects of Tai Chi practice by analyzing the potential cerebral activity changes induced by Tai Chi and their correlation with clinical variables. The study will provide a new approach for investigating the mind-body exercise, and the results might deepen our knowledge about Tai Chi.

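### The plan asks whether Tai Chi acts differently in FC patients and healthy subjects, but no clinical test it names compares the change in one group with the change in the other

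*Protocol article*

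**What the plan says.** The Introduction poses the question directly: "Does Tai Chi have different gastrointestinal modulation effects between patients with gastrointestinal disorders and HS". It then states that "the relatively specific effects of Tai Chi are disease-oriented", in contrast to nonspecific effects on motor and respiratory function. Aim 2 is to "investigate the specific effects of Tai Chi from three aspects, including gastrointestinal symptom, autonomic nervous activity, and emotional state". Aim 1 compares the influence of practice on motor and respiratory function between the two groups.

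Section 2.10.1 fixes two comparisons for continuous clinical data:

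- Between groups: "The clinical data in the two groups (FC group and HS group) will be compared with two-sample" t-tests. The variable (baseline, post or change) is not named.
- Within groups: "the comparisons of the baseline and after intervention in each group will be compared with a paired sample" t-test.

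The Discussion describes the between-group comparison as differences in motor function, respiratory function, "gastrointestinal symptoms, psychological manifestations, and HRV between FC patients and HS after Tai Chi practice". The article nowhere names a change score, a group-by-time term or a baseline-adjusted comparison for the clinical data.

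**The concern.** Whether an effect is disease-oriented is a question about two changes: FC change minus HS change. Two separate paired tests do not answer it. A significant result in one group and a non-significant result in the other is not evidence that the two changes differ.

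A comparison of levels after practice can point the wrong way. If Tai Chi brings FC patients fully up to the HS level, no difference remains to be found. If it acts equally in both groups, the baseline gap survives and is what the test detects.

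At stake is the trial's main interpretive claim. A shared effect could be reported as specific to FC, or a real normalisation, for example of heart rate variability (HRV), could be missed. The same gap affects aim 1, because comparing the influence of practice between groups is also a comparison of changes.

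**Working it through.** **Inputs from the article.** Section 2.2 gives 36 per group, 10% drop-out, 40 recruited per group, and a CSBM change of 1.67 with SD 0.89 from 10 FC patients. Section 2.10.1 gives p < 0.05.

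**Assumptions.** Two-sided tests, normal data, independent groups, and equal SDs in the two groups. The effect sizes, baseline gaps and pre-post correlations below are also assumed, because the article gives none for the FC-HS contrast.

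**Step 1: the plan's own figure.** The noninferiority margin is not given, so 36 cannot be derived from the stated inputs alone. With an assumed margin of 0.5 CSBM per week and one-sided 0.05: N = [0.89 × (1.645 + 0.842) / (1.67 − 1.8 + 0.5)]² = 35.77, rounded up to 36. Then 36/0.90 = 40. This calculation concerns FC alone, not an FC-HS contrast. I take only n = 36 from it.

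**Step 2: two paired tests, same true change in both groups.** Let d be the true change in SDs of change, and p the power to show improvement (noncentral t, 35 df, noncentrality d√36). The groups are independent, so P(significant in FC, not in HS) = p(1 − p) and P(verdicts disagree) = 2p(1 − p).

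| d | p | FC only | Verdicts disagree |
|---|---|---|---|
| 0.2 | 0.214 | 17% | 34% |
| 0.3 | 0.417 | 24% | 49% |
| 0.4 | 0.646 | 23% | 46% |
| 0.5 | 0.831 | 14% | 28% |
| 0.6 | 0.938 | 6% | 12% |

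Worked line for d = 0.3: 0.417 × 0.583 = 0.243. The product p(1 − p) cannot exceed 25%, and d = 0.3 to 0.4 lies near that peak. In 20,000 simulated trials at each d from 0.2 to 0.5, FC-only rates were 16%, 24%, 23% and 14%. A direct two-sample test on change rejected in about 5% of the same trials, which is its nominal rate.

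**Step 3: level test after practice, equal change in both groups.** The baseline gap g (in SDs) is carried through unchanged. The two-sample t-test has 70 df and noncentrality g√(36/2). Rejection rates are 55% for g = 0.5, 92% for g = 0.8 and 99% for g = 1.0. The effect is identical in both groups in every case.

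**Step 4: level test after practice, gap fully closed.** If FC patients start 0.5 SD from HS and practice removes the whole gap, the post-practice means are equal and the level test rejects in 5%. A test of change works with a standardised difference of 0.5/√(2(1 − r)), where r is the pre-post correlation:

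| r | Standardised difference | Change test rejects |
|---|---|---|
| 0.2 | 0.40 | 38% |
| 0.3 | 0.42 | 42% |
| 0.5 | 0.50 | 55% |
| 0.7 | 0.65 | 77% |
| 0.8 | 0.79 | 91% |

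**The case against.** **The text does not say levels.** This stands in part. The between-group sentence in 2.10.1 leaves the variable open, and a t-test on change would fit it. Aim 1's reference to the influence of practice even leans that way. A reader might infer that the plan expressly restricts the comparison to post-practice levels. It does not. That reading is an inference, though a well-supported one: the Discussion places the contrast after practice, 2.10.2 words the imaging contrast the same way, and 2.10.1 attaches before-and-after comparison only to the within-group test. A detail left to a statistical analysis plan would be no finding. Here, however, the article names the tests, and those tests as worded do not settle its central question.

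**The paired test in FC already serves aim 2.** This also stands in part. Section 2.7.1 locates the specific effects for FC patients in symptom relief and autonomic regulation, and the paired test shows whether those outcomes change. A reader might conclude that aim 2 is wholly untested; that goes too far. What lacks a test is the claim that the change is oriented to the disease, which needs the contrast with HS.

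**No rule says that significance in FC only means a specific effect.** True. The rates in Step 2 describe what happens if the results are read that way. The plan offers no other before-and-after contrast to read instead.

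**The sizes depend on chosen inputs.** True, which is why the tables cover a range. The FC-only rate falls to 6% at 0.6 SD. The direction of the error does not depend on the inputs.

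**A change contrast has its own weakness on gastrointestinal outcomes.** This stands in full. FC patients must have fewer than three CSBMs per week and a CCS above 10 (2.3.1), while HS must be free of gastrointestinal symptoms (2.4.2). Regression to the mean favours FC, and HS have little room to improve. Both groups receive Tai Chi and there is no untreated arm. A reader might take a significant difference in change on these outcomes as proof of a disease-oriented effect; this design cannot supply that proof.

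**Conclusion.** The concern holds in a limited form. The article asks whether Tai Chi's effect differs between FC and HS, and no named clinical test compares the two changes. The gap covers the disease-oriented part of aim 2 and the between-group comparison in aim 1. It does not cover whether FC patients change at all.

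With 36 per group and equal true change, a false FC-only pattern arises in about 6% to 24% of trials per outcome over 0.2 to 0.6 SD. If levels after practice are what is compared, an untouched 0.5 SD gap is declared significant in 55%, and a fully closed gap is missed in 95%. Only the sample size is the plan's; the effect sizes and gaps are assumed.

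A change contrast is most informative for HRV and emotional state. For gastrointestinal outcomes it is needed but not sufficient. Emotional state is listed under specific effects in aim 2 but under nonspecific effects in 2.7.1 and 2.7.2, and these sections should be reconciled.

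**What to change.** 1. In 2.10.1, state that FC and HS are compared on post minus baseline, reported as a difference in mean change with a 95% CI.
2. A mixed model with a group-by-time term is an option for outcomes also measured at week 5. It is not available in that form for HRV, which is measured only at baseline and the end (2.7.3, Table 1).
3. State that the within-group paired tests are descriptive for the specific-versus-nonspecific question.
4. In the Discussion, replace the comparison after practice with differences in change.
5. For gastrointestinal outcomes, state that a larger change in FC may reflect regression to the mean or lack of room to improve in HS, and does not by itself establish a disease-oriented effect.

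The cost is wording only, since baseline and end-of-intervention measurements are already scheduled. The downside is precision. With equal SDs, the standard error of a difference in change is √2 times that of one group's change. At 36 per group and two-sided 0.05, the difference detectable with 80% power is √(2/36) × (1.960 + 0.842) = 0.66 SD, against √(1/36) × (1.960 + 0.842) = 0.47 SD for a single group's change. If the SD of CSBM change were 0.89 in both groups (the HS value is assumed), 0.66 SD is 0.59 CSBM per week. The CI should therefore carry the interpretation, and a non-significant difference should not be read as an equal effect.

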#### 2.10.2. Functional MRI Data Analysis

For fMRI scans, all preprocessing steps will be performed using DPABI software based on MATLAB. The main analytical methods include the amplitude of low-frequency fluctuation amplitude (ALFF) and seed-based functional connectivity.

After preprocessing the data, the ALFF will be calculated to compare the whole-brain spontaneous activity pattern before and after intervention in each group, as well as between patients with FC and HS following 10-week Tai Chi practices. The different regions obtained at ALFF analysis will be selected as the region of interest (ROI), also called seed, to perform the seed-based functional connectivity analysis and to explore the functional synchronization of ROI and other regions. The thresholds of *p* < 0.05 with a false discovery rate correlation will be applied to all analyses.

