## 2. Methods and Analysis

### 2.1. Study Design

The trial is designed as a neuroimaging trial that focuses on specific and nonspecific effects of Tai Chi and its potential central responses. A total of 40 FC patients and 40 HS will be recruited. Fifteen participants in each group will be randomly selected to undergo MRI scan. The study procedure is outlined in Figure 1.

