### 2.8. MRI Data Acquisition

MRI data will be collected on 15 participants in each group at the baseline and the end of intervention. The acquisition parameter will be consistent with our previous article [15].

The MRI scan includes three sequences: a high-resolution 3-dimensional T1-weighted imaging (3D-T1W1), a blood oxygenation level-dependent functional MRI (BOLD-fMRI), and a diffusion tensor imaging (DTI) sequence. Scanning will start in the morning after overnight fasting. Subjects who are selected will undergo MRI scan with a 3.0 T magnetic resonance scanner (Siemens, Germany). The 3D-T1WI scan parameters will be as follows: repetition time/echo time: 1900 ms/2.26 ms; slice thickness: 1 mm, slice number: 176, matrix size: 128 × 128, and the view field: 256 × 256 mm^2^. The BOLD-fMRI scanning parameters are as follows: repetition time/echo time: 2000 ms/30 ms; flip angle: 90°; slice number: 30; matrix size: 128 × 128; view field: 240 × 240 mm^2^; slice thickness: 5 mm; and total volume: 240. DTI data are as follows: view field: 240 × 240 mm^2^; repetition time/echo time: 6800 ms/93 ms; matrix size: 128 × 128; and slice thickness: 3 mm, seamless. Two diffusion-weighted sequences will be acquired using gradient values b: 1000 s/mm^2^ and b: 0, with diffusion-sensitizing gradients used in 64 noncollinear directions.

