### 3.1. Specific and Nonspecific Effects of Tai Chi

Tai Chi is a complex sport that requires the coordination of spirit, breathing, postures, and movements. It can produce a significant impact on almost all human systems such as motor system, cardiovascular system, respiratory system, and digestive system. The impact is far beyond the physiological and psychological changes brought by a simple physical exercise. Thus, Tai Chi is not only widely used in public healthcare but also involved in disease treatment and rehabilitation.

On the basis of the characteristics of Tai Chi and related studies, we put forward that there are two types of effects of Tai Chi. One is the specific effect, which mainly indicates the therapeutic effects of Tai Chi practice on the pathological status and has obvious disease orientation. For instance, Tai Chi practice could produce a specific-regulating effect on the abnormal gastrointestinal (GI) function of patients with GI disorders, specifically improve the cognitive function of patients with Alzheimer's disease [26], and significantly relieve the depression symptoms of patients with depression [27]. A systematic review and meta-analysis demonstrated that Tai Chi and other mind-body interventions were effective in alleviating GI symptoms and improving several aspects of the disease-related QOL including interference with activity, body image, health worry, food avoidance, and social reaction [10].

The second aspect is the nonspecific effects, which mainly refers to the benefits for the motor system, respiratory system, and others. No matter Tai Chi practice or other forms of physical exercises can produce it. The nonspecific effects might be a promoting effect on the motor system and respiratory system for not only the patients but also the HS. For example, studies demonstrated that Tai Chi exercises could increase the muscle strength in the lower extremities, improve balance control, and reduce the risk of falls for both healthy elderly people [28, 29] and Parkinson's and stroke patients [30, 31]. However, it should be emphasized that the specific effects of Tai Chi are relative and conditional. The nonspecific effects are the more widely used and fundamental effect of Tai Chi.

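### The imaging plan tests ALFF change within each group of 15 and compares FC with HS, but has no test of change common to both groups, so the nonspecific central response in aim 3 cannot be directly established

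*Protocol article*

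**What the plan says.** Section 2.1 sets the imaging sample: "Fifteen participants in each group will be randomly selected to undergo MRI scan". Section 2.8 fixes two scans per person: "MRI data will be collected on 15 participants in each group at the baseline and the end of intervention". Each scanned participant therefore contributes one before-after change.

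Section 2.10.2 names two ALFF contrasts. The first compares whole-brain activity "before and after intervention in each group". The second is "as well as between patients with FC and HS following 10-week Tai Chi practices", which reads as a comparison of values after the intervention. The regions found are then carried forward: "The different regions obtained at ALFF analysis will be selected as the region of interest (ROI), also called seed". An FDR threshold of 0.05 applies throughout.

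The aims ask for more than these contrasts give. Aim 3 in the Introduction covers central responses of both the specific and the nonspecific effect, and the Discussion repeats that the study tries to "explore the potential central mechanism of the specific and nonspecific effects of Tai Chi practice". Section 3.1 describes the nonspecific effect as a benefit to the motor and respiratory systems "for not only the patients but also the HS". Section 2.10.3 adds correlations of motor, respiratory and psychological data with cerebral function in FC patients and HS.

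**The concern.** A nonspecific central response, if it parallels the nonspecific effect in section 3.1, is a change present in both groups. The within-group contrast asks about one group at a time. The between-group contrast asks where the groups differ. No contrast asks where they change together, so half of aim 3 has no matching test.

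The available substitutes are weak. Setting two separately thresholded maps of 15 side by side has low power to show a shared region in both. It also invites the error of treating significance in one map but not the other as a group difference. The FC-versus-HS comparison does not repair this. As worded it uses post-intervention values, and section 3.2 itself cites baseline brain differences between FC patients and healthy controls, so a difference after 10 weeks may have been there before. Even a null difference in change would not show that both groups changed.

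At stake is the distinction between specific and nonspecific effects, which the trial is built on, and the choice of seeds for the connectivity analysis.

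**Working it through.** **No imaging figure to reproduce.** The protocol gives no power calculation for the 15 per group. The sample size in section 2.2 concerns bowel movements and is not an input here.

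**Inputs from the documents.** 15 FC and 15 HS; one before-after change per person; FDR 0.05.

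**Assumptions.** The true standardised change d is equal in both groups, with d from 0.5 to 1.5. Tests are two-sided. Voxel thresholds of p<0.001 and p<0.005 stand in for the FDR cut-off.

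**Formulas.** Power of one map is p = P(T > t_crit), where T is noncentral t with 14 df and noncentrality d√15. The pooled main effect of time has 28 df and noncentrality d√30. For independent groups, both maps = p², exactly one = 2p(1−p), neither = (1−p)².

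**Worked case, d = 0.8, p<0.001.** Noncentrality is 0.8 × √15 = 3.10, giving p = 0.223. Both = 0.223² = 0.050. Exactly one = 2 × 0.223 × 0.777 = 0.346. Neither = 0.777² = 0.604. Pooled: 0.8 × √30 = 4.38, power 0.747.

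| d | threshold | one map | both | exactly one | neither | pooled (30) |
|---|---|---|---|---|---|---|
| 0.5 | 0.001 | 4.5% | 0.2% | 8.5% | 91% | 21% |
| 0.5 | 0.005 | 13% | 1.7% | 22% | 76% | 40% |
| 0.8 | 0.001 | 22% | 5% | 35% | 60% | 75% |
| 0.8 | 0.005 | 45% | 20% | 49% | 31% | 90% |
| 1.0 | 0.001 | 44% | 20% | 49% | 31% | 95% |
| 1.0 | 0.005 | 70% | 49% | 42% | 9% | 99% |
| 1.2 | 0.001 | 68% | 46% | 44% | 10% | >99% |
| 1.2 | 0.005 | 88% | 77% | 21% | 1.5% | >99% |
| 1.5 | 0.001 | 92% | 84% | 16% | 0.7% | >99% |
| 1.5 | 0.005 | 98% | 97% | 3% | <0.1% | >99% |

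**Check under FDR itself.** Benjamini–Hochberg at 0.05 was simulated over 5,000 independent regions, with 5–20% truly changed equally in both groups. The pooled test found 83–94% of shared regions at d = 0.8, against 2–18% found in both maps. At d = 1.0 this was 98–99% against 23–59%; at 1.2, about 100% against 61–87%; at 1.5, 100% against 93–99%. Among shared regions found in at least one map, the share found in only one was 73–94% at 0.8, 38–68% at 1.0, 13–36% at 1.2 and 1–7% at 1.5. Spatial correlation would alter these figures.

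**Check of the labelling rule.** A pooled effect can come from one group alone. For a region that changes only in FC (d = 1.2 to 1.5, none in HS), pooled significance plus the same sign in both groups would call it nonspecific 29–48% of the time. Requiring p<0.05 in each group as well cuts this to about 2.5%, because the unchanged group passes in the right direction only 2.5% of the time. The stricter rule still finds 63–67% of shared regions at d = 0.8; its ceiling there is the chance that both groups reach p<0.05, 0.821² = 67%.

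**The case against.** The strongest defence has four parts.

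- **Exploratory aim, condensed text.** Aim 3 is exploratory, and section 2.10.2 lists its main methods without claiming to be complete. Further contrasts may sit in a fuller plan. This limits how serious the point is. However, the article does name the contrasts, the threshold and the seed rule, and those contrasts do not match the aim.
- **Another route exists.** Section 2.10.3 links nonspecific effects to cerebral function by correlation, so it would be wrong to say that comparing maps is the only route. But a region could change by the same amount in everyone and correlate with nothing, so correlation does not test shared change.
- **The misreading is not documented.** A reader might infer that the investigators will use map overlap, or will call a region specific because it survives in one group only. The text says neither, and it does not label seeds as specific or nonspecific.
- **The definition is not explicit.** Section 3.1 speaks of motor and respiratory benefit. It does not say that the nonspecific brain response must be the same region in both groups. That step is an interpretation, though some test of common change is needed before a central response can be called nonspecific.

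A reader might also infer that shared regions will usually look group-specific. The figures do not support this. Over all shared regions, 2p(1−p) cannot exceed 50%. At 0.8 SD and p<0.001 the commonest result is detection in neither map (60%). At 1.0 SD and p<0.005, both maps (49%) overtakes exactly one (42%). Being seen in only one map is the majority result only among regions detected at all, and only when single-map power is below two thirds.

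**Conclusion.** The gap holds whatever the effect size: no planned imaging contrast tests change common to FC patients and HS, so the nonspecific part of aim 3 cannot be directly established.

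The practical loss depends on an effect size that the documents do not give. It is large at about 0.8 SD and mixed at 1.0 SD. At 1.2 SD it is much reduced under FDR, though still visible at a strict voxel threshold, and by 1.5 SD it is small. At 0.5 SD even the pooled test has only 21–40% power, so the fix does not rescue small effects. All figures assume equal change in both groups and no dropout among the 30 scanned. The supportable statement is that a shared region of moderate effect is likely to appear in only one map or in neither.

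**What to change.** In section 2.10.2:

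1. Analyse ALFF in a group-by-time model over all 30 scanned participants, at the same FDR threshold.
2. Use the main effect of time to find candidate common regions.
3. Use the group-by-time interaction, which compares change and not post-intervention values alone, for group-specific regions.
4. Call a region nonspecific only if the main effect survives and each group also changes in the same direction at p<0.05 within that region. Report both group estimates.
5. State that survival in one group's map alone does not show specificity.

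The cost is a little more analysis on scans already planned, with no new participants or visits. Requiring change in each group costs some sensitivity: about 63–67% of shared regions are found at 0.8 SD, against 75–90% for the pooled test alone. In return, a region that changes in one group only is rarely labelled nonspecific.

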### 3.2. Potential Central Responses of Tai Chi

As a typical physical and mental exercise, Tai Chi not only emphasizes physical movement but also requires the state of unity of body and mind. The positive effects of meditation and aerobic exercise on cognitive function, including memory and decision-making abilities, have been widely accepted [32, 33]. Recent studies further identified the influence of Tai Chi practice on the cerebral structure and function of practitioners [34]. For example, MRI studies showed that Tai Chi training evoked significant changes in the brain white matter network [35], brain volume [36], and spontaneous brain functional activities [37] in older people. These studies indicated that Tai Chi practice could influence not only the cerebral function but also the brain structure. It might be the central mechanism of the specific and nonspecific effects of Tai Chi.

In this study, FC patients will be enrolled to investigate the specific effects of Tai Chi-modulating GI function. FC, as a typical FGID, the dysfunction of the gut-brain axis plays an essential role in its pathogenesis [38]. Recent neuroimaging studies identified the abnormality in the cerebral function and structure in FC patients compared with the healthy controls. For example, an fMRI study demonstrated that FC patients showed significant differences in baseline brain activities in several brain regions implicated in emotional process modulation, somatic and sensory processing, and motor control regions [39]. Considering the existence of cerebral structural and functional abnormalities in FC patients, it is feasible to explore the mechanism of Tai Chi's specific effects on GI function of FC patients.

In this study, fMRI will be selected as the neuroimaging technique to investigate the cerebral activity changes elicited by Tai Chi practice. fMRI is the most commonly used brain imaging technique and has been widely used in the studies on the central mechanism of Tai Chi intervention [35, 40, 41]. For example, using fMRI, people found that influencing the resting-state functional connectivity alteration between the cognitive control network and rostral anterior cingulate cortex and medial prefrontal cortex might be the central mechanism of Tai Chi intervention for fibromyalgia [41]. These studies indicated that it was reliable to use fMRI to explore the central mechanism of Tai Chi intervention for FC.

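### The only planned between-group ALFF contrast is post-intervention, so it and any seeds drawn from it cannot separate pre-existing FC differences from a differential response to Tai Chi

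*Protocol article*

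**What the plan says.** Section 2.10.2 names two ALFF comparisons. The first will "compare the whole-brain spontaneous activity pattern before and after intervention in each group". The second is given as "as well as between patients with FC and HS following 10-week Tai Chi practices". No baseline comparison of FC with HS is stated, nor a between-group comparison of change or a baseline adjustment. The same section sets a threshold of p < 0.05 with false discovery rate (FDR) control and then says: "The different regions obtained at ALFF analysis will be selected as the region of interest (ROI), also called seed". It does not say which of the two ALFF contrasts supplies these seeds.

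Section 2.8 states that "MRI data will be collected on 15 participants in each group at the baseline and the end of intervention". Table 1 and the text below it agree. The Abstract mentions fMRI only at the end of practice, but the before/after comparison needs both scans.

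Section 3.2 reports that an "fMRI study demonstrated that FC patients showed significant differences in baseline brain activities in several brain regions", compared with healthy controls. It makes this a premise of the design: "Considering the existence of cerebral structural and functional abnormalities in FC patients".

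Aim 3 in the Introduction is to explore the central responses behind Tai Chi's specific and nonspecific effects. The Discussion speaks of cerebral changes that Tai Chi induces.

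**The concern.** FC and HS are groups defined by disease status, and both practise Tai Chi. Randomisation decides only who is scanned, so nothing makes the two groups alike in ALFF at the start. The protocol itself expects them to differ.

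A map of FC against HS at week 10 alone therefore contains whatever difference was there at week 0. If that map is used for Aim 3, regions that mark constipation could be reported as regions that respond to Tai Chi. If its regions become seeds, the same ambiguity passes into the connectivity analysis. The scans needed to avoid this are already planned, but this contrast does not use them.

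**Working it through.** The plan gives no power or effect-size figure for the imaging, so there is no figure of its own to reproduce. The check has two parts.

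**1. What each contrast estimates.** For one region, write the mean ALFF as F0 and F1 in FC and H0 and H1 in HS, with 0 for baseline and 1 for the end of practice.

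- Post-only group contrast: F1 − H1 = (F0 − H0) + [(F1 − F0) − (H1 − H0)]. This is the baseline difference plus the difference in change.
- Within-group contrasts: F1 − F0 and H1 − H0. A stable baseline difference cancels. Each is tested against zero in its own group, so significance in one group and not in the other is no test of whether the two changes differ.
- Group-by-time contrast: (F1 − F0) − (H1 − H0). The baseline difference cancels and the differential change is tested directly. This contrast is not planned.

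**2. Illustration of size.** Inputs:

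- n = 15 per group (sections 2.1 and 2.8).
- Two-sided 0.05 at a single region. The level is from section 2.10.2; two-sidedness is assumed because it is not stated; no FDR correction is applied here.
- A stable baseline difference of d SD, assumed at 0.5 to 1.2. The documents give no value.
- True Tai Chi effect zero in both groups.
- Baseline-to-end correlation 0.5 or 0.7, also assumed.

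The post-only two-sample t-test has 28 degrees of freedom and noncentrality d × √(n/2) = d × √7.5 = 2.739 d. The exact rejection rate comes from the noncentral t distribution. The change comparison was simulated with 20,000 runs per setting. Ranges cover the two correlations.

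| Assumed d | Noncentrality | Post-only, exact | Post-only, simulated | Change between groups, simulated |
|---|---|---|---|---|
| 0.5 | 1.37 | 26.2% | 25.9–26.6% | 4.9% |
| 0.8 | 2.19 | 56.2% | 56.2–56.3% | 5.0% |
| 1.0 | 2.74 | 75.3% | 75.2–75.5% | 4.9–5.1% |
| 1.2 | 3.29 | 88.7% | 88.7–88.8% | 4.6–5.1% |

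The paired before/after test in FC was significant in 4.9% to 5.2% of runs, which confirms that the within-group contrast is not disturbed by a stable baseline difference.

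FDR control has no fixed per-region level. As a rough guide to a stricter threshold, the exact post-only rates at an assumed two-sided level of 0.001 are 2.0%, 9.6%, 20.9% and 37.6% for the same four values of d. The rates fall, but FDR does not cure the problem: the baseline difference is real, so finding it is a correct answer to a different question.

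**The case against.** Several points on the other side are sound and limit the finding.

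- **The within-group contrasts already address Aim 3.** This stands in part. They use the baseline scans, match the stated interest in changes induced by Tai Chi, and are the right place to look for effects common to both groups. A reader might infer that Aim 3 as a whole would be answered by disease-related regions; the documents do not support that. What remains open is whether FC and HS change differently.
- **No rule says that the FC–HS map will be read as a Tai Chi response.** Correct. That reading is an inference from Aim 3 and the Discussion. A post-treatment comparison of patients with healthy subjects could also be meant as a description of the remaining difference.
- **Contaminated seeds are possible, not established.** Correct. Seeds may come from either contrast, and section 2.10.3 does not tie its correlations to these seeds. But nothing restricts seeds to the before/after maps.
- **The percentages are not those of the planned test.** Correct. They are single-region rates before FDR correction, under assumed differences, and whole-brain rates would probably be lower.
- **The article is condensed and the imaging aim is exploratory.** Also true, and the sample size rests on bowel movements. Yet the article does not leave this contrast open: it names the groups and the time point. If a comparison of change was meant, one sentence would settle it.

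**Conclusion.** The point holds for the between-group ALFF contrast and for any seeds taken from it. As written, that contrast cannot distinguish a pre-existing FC difference, which the protocol says exists, from a differential response to Tai Chi. It does not extend to the within-group contrasts, and it does not show that the seed or correlation analyses are necessarily biased.

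The true size is unknown because the documents give no ALFF difference between FC and HS. With no Tai Chi effect at all and assumed stable differences of 0.5, 0.8 and 1.0 SD, the post-only test would flag a region in about 26%, 56% and 75% of trials at an uncorrected 0.05, against about 5% for a comparison of change. The conclusion about what the contrast estimates does not depend on those figures; it follows from the decomposition in the working.

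**What to change.** Reword section 2.10.2 as follows.

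1. Make the between-group ALFF contrast a comparison of pre-to-post change between FC and HS (group-by-time), at the same FDR threshold.
2. Take seeds for the Tai Chi response only from the group-by-time and within-group change maps, and compare connectivity between groups on change as well.
3. Report the baseline and post-only FC–HS maps, labelled as descriptive.
4. Keep the within-group before/after contrasts for effects shared by both groups, which a group-by-time contrast cannot show.
5. State the limit: both groups practise Tai Chi and there is no untreated arm, so the interaction shows differential change. It cannot by itself rule out natural change in symptomatic patients or other time effects that differ between the groups.

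The cost is analysis wording only. Both scans are already planned in the same participants, so no extra scan or recruitment is needed. The change should be made before the imaging data are analysed.
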